**Personal information**		
Gender, school year, age, DOB, place of birth, ethnicity and cohabitants	DE	Adapted from general household survey [61]
Family affluence	DE	Family affluence scale [62,63]
**Substance use**		
Ever smoked?	CV	One question from substance initiation index [29]
Smoking status	CV	ASSIST study version of NatCen/NFER question [64]
Ever drunk a drink?	CV	NatCen/NFER [65]
Age of first drink?	CV	NatCen/NFER [65]
Frequency of drinking	CV	NatCen/NFER [65]
Ever little drunk?	CV	Adapted from HBSC questionnaire
Little drunk in last 3 months?	CV	Adapted from HBSC questionnaire
Ever really drunk?	CV	Adapted from HBSC questionnaire
Really drunk in last 3 months?	CV	Adapted from HBSC questionnaire
Ever taken drugs	CV	Adapted from HBSC / NatCen/NFER
**Behaviour**		
Strengths and difficulties	CV	SDQ [66]
Aggressive and destructive conduct	CV	From Spoth, et al. [28]
**Life at home**		
Things in your bedroom	CV	Adapted from young people, new media survey [67,68]
TV, computer games, computer use	CV	From HBSC questionnaire
Free time activities	CV	Modified questions from west of Scotland twenty-07 study
Family functioning	CV	Family relationship index [69,70]
Parenting/child management	CV	General child management, project family [71,72]
Parents and school	CV	Three questions, one of which is adapted from the child rearing practices measure
Family activities	CV	From HBSC questionnaire/PEACH study
**General health**		
Sleep – difficulties	CV	From HBSC questionnaire
Getting up/bedtimes	CV	From PEACH study
Health state today	CV, HE	EQ-5D [73]
General health	CV	Kidscreen 27 [74]

**Key**: **CV** = Covariate; **HE** = Health Economics; **DE** = Demographics; **IO** = Immediate outcome; **ST** = Short term outcome; **PO** = Primary outcome; **SO** = Secondary outcome; **TO** = Tertiary outcome.

**Table 3 T3:** Measures collected at baseline from parents/carers

**Domain/question topic**	**Purpose**	**Source**
**Personal information**		
Place of birth, relationship status, ethnicity, qualifications,	DE	Adapted from general household survey [61]
Employment	DE	NS-SEC
Co-habitants	DE	Adapted from GHS [61]
**Substance use**		
Smoke (Y/N)	CV	
Cigarettes smoked per day	CV	Heaviness of smoking index [75]
Frequency of drinking	CV	Adapted from AUDIT-C [76]
Number of drinks consumed when drinking	CV	Adapted from AUDIT-C [76]
Frequency of drinking 6+ drinks in a row	CV	Adapted from AUDIT-C [76]
Ever used drugs	CV	Adapted from HBSC/NatCen/NFER [65]
**Child’s substance use**		
Has child ever smoked?	CV	Question adapted from substance initiation index [29]
Does child smoke now?	CV	Adapted from NatCen/NFER [65]
Has child ever had a drink?	CV	Adapted from NatCen/NFER [65]
Has child ever been drunk?	CV	Developed by project SFP Cymru research team
Has child ever used drugs?	CV	Adapted from HBSC/NatCen/NFER [65]
**Strengths and difficulties**		
Strengths and difficulties	CV	SDQ [66]
**Section 6**		
Free time – use of TV, computer, etc.	CV	From HBSC questionnaire
Family activities	CV	From HBSC/11-16 West of Scotland adult questionnaire
Family functioning	CV	Family relationship index [69,70]
Parenting/child management	CV	General child management measure, project family [71,72,77]
Parent–child bonding	CV	Adapted from Spoth’s rural urban cumulative risk index and Arthur, et al. [78,79]
Parents and school	CV	Questions developed by project team and one from Conger’s child rearing practices measure
**Measures of health status**		
Health status	HE	GHQ-12 [80,81]
Health	HE	1 item from SF-36 [82]
Health state today	HE	EQ-5D [73]

**Table 4 T4:** Measures collected at 9 and 15 month follow-up from parents/carers

**Domain/question topic**	**Purpose**	**Source**
**Life at home**		
Parenting/child management	IO	General child management measure, project family [71,72,77]
Parent–child bonding	ST	Adapted from Spoth’s rural urban cumulative risk index and Arthur, et al. [78,79]
Parents and school	ST	Questions developed by project team and one from Conger’s child rearing practices measure
Parental expectations	IO	Adapted from ALSPAC study/developed by project SFP Cymru research team
Participation in household tasks	IO	Adapted from ALSPAC/developed by project SFP Cymru research team
**Service utilisation**		
Health service utilisation	HE	Adapted from ALSPAC
Social care for adults	HE	Adapted from ALSPAC
Social care for children	HE	Adapted from ALSPAC
Criminal justice	HE	Adapted from ALSPAC

**Table 5 T5:** Measures collected at 24 month follow-up from young people

**Domain/question topic**	**Purpose**	**Measure/source**
**Behaviour - strengths and difficulties**		
Strengths and difficulties/wellbeing and stress	TO	SDQ [66]
**Life at home**		
Family activities (opportunities for involvement in pro-social activities; possibly bonding)	ST	From HBSC/PEACH study
Young people’s own time		From west of Scotland Twenty 07
Parenting/child management	IO/	General child management measure, project family [71,72,77]
	TO	
Parents and school		Three questions; one adapted from the child rearing practices measure
Help around the home	IO	Adapted versions of questions asked to parents at 9/15 months.
Development of self-efficacy	ST/ TO	Bandura’s self efficacy scale [83]
Attachment to parents	ST	The security scale [84]
Befriending pro-social/anti-social peers	ST	Social development model scale on friends’ anti-social qualities (Interaction with antisocial peers scale) [85]
Positive bonding to school	ST	School bonding measure/SDM [86]
**Participant substance use**		
Smoking behaviour – ever smoked?		Question from substance initiation index [29]
Smoking status	TO/ SO	ASSIST study version of NatCen/NFER question [64]
Age first smoked	TO	From HBSC questionnaire
Ever drunk a drink?		NatCen/NFER [65]
Age of first drink	SO	Adapted from HBSC/NatCen/NFER
Drinking frequency, last month (including different types)	SO	Adapted questions from HBSC questionnaire
Ever really drunk?		From HBSC questionnaire
Age first drunk		Adapted version of question in HBSC questionnaire
Number of times drunk, drinking alcohol or 5+ drinks in a row in last month	PO/SO	Adapted from HBSC questionnaire
Alcohol-related problems	SO	Q21 from ESPAD survey [87]
Drug use – ever used?		Amended from HBSC/NatCen/NFER [65]
Cannabis use (ever, 12 months, or 30 days)	SO	From HBSC questionnaire
Age of first drug use	TO	Adapted from HBSC questionnaire
**General health**		
Health state today	HE/TO	EQ-5D (child version) [73]
General health	HE/TO	UK Kidscreen 10 [74]

**Table 6 T6:** Measures collected at 24 month follow-up from parents/carers

**Domain/question topic**	**Purpose**	**Source**
**Section 2 – consent**		
**Life at home**		
Family activities		From HBSC/11-16 West of Scotland adult questionnaire
Family functioning	TO	Family relationship index [69,70]
Parenting/child management	IO	General child management measure, project family [71,72,77]
	SO	
Parent–child bonding	ST	Adapted from Spoth’s rural urban cumulative risk index and Arthur, et al. [78,79]
Parents and school		Question developed by project team and one from Conger’s child rearing practices measure
**Participant substance use**		
Smoking behaviour		Heaviness of smoking index [75]
Alcohol use		Adapted AUDIT-C questions, as used by Pre-empt study [76]
Drug use		Adapted from HBSC/NatCen/NFER [65]
**Health**		
Health status	HE	GHQ [80,81]
	TO	
Health	HE	1 item from SF-36 [82]
Health state today	HE	EQ-5D [73]
	TO	
**Service utilisation**		
Health, social care, education and criminal justice service utilisation	HE	Modified from ALSPAC

### Assessments and data collection

#### Baseline

Computer assisted personal interviews (CAPIs) are conducted by research fieldworkers with parents/carers and children. Children’s baseline CAPIs cover: substance use behaviours, and aggressive and destructive behaviour; strengths and difficulties (using the Strengths and Difficulties Questionnaire); health, and sleeping patterns. Five sets of questions assess aspects of participants’ home life, namely: possessions the participants have in their bedroom; family activities and free time activities; family functioning; and parenting/child management. Full details are provided in Table 
2.

Parent/carer interviews cover: drug and tobacco use, and parental reports of children’s substance use; parent–child bonding; parenting and family relationships and activities: and parents/carers’ health status. Participants also complete the parent version of the Strengths and Difficulties Questionnaire (SDQ). Table 
3 provides a full list of questions and measures included in the interviews.

### Follow-up

#### 9 and 15 months

Parents/carers are followed up at 9, and 15 months past baseline, using computer aided telephone interviews (CATIs) conducted by the Participant Resource Centre at Cardiff University. Interviews at 9 and 15 months (Table 
4) are identical, and collect data on hypothesised short term and intermediate outcomes. Baseline measures of parent–child bonding and parenting/child management are repeated. Parental expectations of their child(ren) and opportunities for the latter to participate in household tasks are assessed. Health, criminal justice and social care services utilisation is captured.

#### 24 months

At two years past baseline CAPIs are conducted by research fieldworkers with parents/carers and children (Tables 
5 and
6). Interviews with parents/carers cover participants’ substance use, health status and health and social care service utilisation. Young people’s interviews repeat baseline measures of smoking, alcohol and drug use. Additional questions examine age of first cigarette, age of first drunkenness, last month drinking frequency (including types of drinks), binge drinking and drunkenness frequency, cannabis use, and alcohol-related problems. The interview also assesses child reports of short term/intermediate outcomes, opportunities for involvement in pro-social activities in participants’ families, and attachment to parents, parenting/child management, and parental involvement in school work/activities. The extent to which young people help around the home is captured using suitably adapted versions of the questions asked to parents at 9/15 months. Other questions assess self-efficacy, school bonding, and interaction with anti-social peers. The child version of the SDQ is also administered. Measures of participants’ health used at baseline are repeated. Saliva samples are collected from consenting young people to assess inhalation of tobacco smoke in the previous few days, using a cotton wool swab of a salivette
[88].

### Sample size

We will aim to recruit 378 families in each arm of the trial (756 families in total). This will provide us with at least 80% power at the 2.5% level (halved to account for our two primary outcomes) to detect either a 12% difference in young people reporting having drunk alcohol (assuming a control group prevalence of 48%
[4]), or a 10% difference in young people reporting having been drunk (assuming a prevalence of 22%
[4]), at two year follow-up. This sample size is based on an average family in the trial having 1.25 young people, an intracluster correlation coefficient (ICC) of 0.2 and is adjusted to allow for 25% loss to follow-up (including withdrawals from the trial by participants prior to 24 month follow-up).

### Analysis

#### Main analysis

The primary analyses will be based on the intention-to-treat principle and will involve fitting two-level logistic regression models to our primary outcomes (reported drinking at two year follow-up and reported drunkenness at two-year follow-up), with responses from young people nested within families. The covariates in the models include those balanced at randomisation (type of family – general population/family with challenges, and average age of young people) and baseline levels of drinking and drunkenness (depending on the outcome). Trial area (used as a stratification variable at randomisation) will be adjusted for. For each primary outcome, a statistically significant result will be concluded if the p-value for the trial arm explanatory variable is <0.025. While our power calculation is based on the above, a combined test will be performed if both p-values lie between 0.025 and 0.05. This will take the correlation of the outcomes into account and provide an overall p-value for the two outcomes.

The primary analyses will also be repeated

• controlling for any baseline imbalances;

• without controlling for any of the above mentioned covariates;

• respecting the original ordinal scale (the primary questions are asked on an ordinal scale ranging from 0 occasions to 40+ occasions) using an ordinal regression model; and

• using a complier average causal effect (CACE) approach, to investigate the treatment effect in the treatment adherent.

Secondary analysis includes investigating the effect of the intervention on substance use (reported use of tobacco and cannabis) at two year follow-up by fitting two-level logistic regression models, controlling for baseline reports of substance use, as well as the variables balanced at randomisation (all models will control for the variables that were balanced on at randomisation). The effect of the intervention on the proportion of young people reporting alcohol-related problems will be analysed similarly. The effect of the intervention on substance initiation (alcohol, tobacco and cannabis) will be investigated by fitting two-level Cox proportional hazards models (young people nested within families) for those participants who had not already initiated at baseline.

Educational achievement at 16 will be compared between trial arms by fitting a two-level logistic regression model (young people nested within families) comparing the proportion of young people who obtain five or more GCSEs at a grade C or above (GCSE Grades use an A*-G scale, with A* being the highest score). The proportion of young people who continue in education beyond 16 will be similarly compared between trial arms by fitting a logistic regression model. This analysis will be performed on the whole sample following the date that all participants (young people) should have completed school Year 11 when GCSEs are normally awarded. Other secondary and tertiary outcomes (e.g. parenting and child management, parent–child affective behaviour and wellbeing and stress) will be analysed by fitting similar regression models, controlling for clustering of responses within families (as appropriate) and controlling for variables that were balanced on at randomisation.

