[59]. These mixed groups demonstrated evidence of high levels of participant retention and acceptability, and social effects outside the programme, with participating families supporting each other between sessions and after the end of the programme. Our trial of the SFP 10–14 UK in Wales (Project SFP Cymru) uses this ‘mixed families’ approach to group recruitment and composition, as well as the fully culturally adapted materials. The trial therefore builds on the completed formative evaluation, adaptation and exploratory evaluation of the UK version of the programme
[47,48,50,51,59], and will generate important new evidence on the programme’s long-term effectiveness and cost-effectiveness in the UK.

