### Recruitment

SFP 10–14 UK will be implemented in seven geographical areas of Wales by local agencies that are independent of the research team (e.g. local authority parenting teams, children’s charities). Trial areas will run the programme on approximately 8 occasions over a two year period, with a maximum capacity of 10–12 intervention families per programme.

SFP 10–14 UK is designed for delivery to families with children aged 10–14, and in the Wales adaptation is targeted towards a mix of children and their families. Each programme is open to families from a loosely defined and fairly large geographical area. In each area, self-referrals to the Programme come forward in response to awareness-raising in community and educational settings. Other referrals come from agencies such as education, health and social services which identify families that may benefit from participating in the Programme.

Potential referrers and families are informed that the Programme is being run as part of a trial and are provided with brief information about the trial. When a family is referred or applies to the SFP 10–14 they will be visited by a member of the programme delivery team (normally the programme coordinator) who will undertake a needs and eligibility assessment. Based on the information contained in the family referral/application form and the needs and eligibility assessment the coordinator determines if eligible families are from the ‘general population’ or a family with challenges (in the context of a group setting). If families are deemed eligible to attend the programme they will be asked if they are willing for a member of the research team to have access to their referral notes and to visit them. Where the family agrees a research fieldworker will then visit them to obtain informed consent to participate in the trial, collect baseline data using a computer assisted personal interview (CAPI), and inform the family of the treatment group (C or I) to which they have been randomised. Figure 
1 shows the anticipated flow of participants through the trial.

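### The primary models and the power calculation allow for clustering within families but not within programme runs, so if the run-level ICC is above zero the 0.025 threshold is not held and the power for drinking has almost no reserve

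*Protocol article*

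**What the plan says.** All references are to the protocol article.

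- **Main analysis.** Both primary outcomes are analysed by two-level logistic regression, "with responses from young people nested within families". Covariates are family type, average age of the young people, and baseline drinking or drunkenness; trial area is also adjusted for. Significance is declared at p < 0.025 per outcome. The four listed repeat analyses vary the covariates, the outcome scale or the estimand. None adds a level above the family. The secondary models keep the same family-only structure.
- **Sample size.** 378 families per arm, 1.25 young people per family, ICC 0.2, 25% loss. The claim is: "This will provide us with at least 80% power at the 2.5% level", for a 12-point difference in drinking from 48% or a 10-point difference in drunkenness from 22%.
- **Recruitment and Intervention.** Seven areas each run the programme about eight times, "with a maximum capacity of 10–12 intervention families per programme". Each run has seven weekly sessions led by a team of professionals.
- **Background.** Earlier mixed groups are described "with participating families supporting each other between sessions and after the end of the programme". The Intervention section again presents mutual support among families as a feature of delivery, and the Discussion calls the mixed-group composition a core part of the model under test.

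**The concern.** Families are randomised one by one, but in the intervention arm they are treated in groups, so the design is partially nested. Young people from different families in the same run share facilitators, sessions and, by the article's own account, continuing contact. If that makes their outcomes alike, a model with only a family level counts them as more independent than they are. The variance of the intervention-arm estimate is then understated, and so is the standard error of the arm effect. The error favours declaring an effect.

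The area terms do not deal with this, because there are about eight runs within each area. Nor is it a detail left to a later analysis plan: the article fixes the levels of the primary model and lists its power inputs, so adding a run level would change what is stated.

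It matters more here because the Background and Discussion criticise earlier trials of the programme for significance claims that may not be justified. The level was also halved to 0.025 specifically to control error over two primary outcomes.

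**Working it through.** **Inputs from the article.** 378 families per arm; 1.25 young people per family; family ICC 0.2; 25% loss; 48% v 36% (drinking) and 22% v 12% (drunkenness), reading each difference as a reduction; level 0.025, taken as two-sided (z = 2.2414).

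**Assumed.** The run-level ICC (ρ), because the article gives none. Runs are taken as equal in size.

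**1. Reproduce the plan's figure.** Drinking, pooled two-proportion formula with continuity correction: 337 young people per arm. Design effect 1 + (1.25 − 1) × 0.2 = 1.05. Then 337 × 1.05 = 353.9; ÷ 1.25 = 283.1 families; ÷ 0.75 = 377.4, that is **378**. Without the correction the result is 359.5. Drunkenness needs only 321 (299 uncorrected), so drinking drives the size.

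**2. Families per run.** 7 areas × 8 = 56 runs gives 378/56 = 6.75. The Process evaluation section caps facilitator reflection sheets at 336. At one sheet per session over seven sessions that implies 48 runs, and 378/48 = 7.9. Analysed young people per run are m = families × 0.75 × 1.25 = 6.33 or 7.38.

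**3. Design effects.** Control arm: 1.05. Intervention arm: 1.05 + (m − 1.25) × ρ. Subtracting 1.25 rather than 1 avoids counting siblings twice.

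**4. True level of the planned test.** α = 2 × [1 − Φ(2.2414 × √(2.10 / (1.05 + DE_int)))].
Example, 6.75 families, ρ = 0.02: DE_int = 1.05 + 5.08 × 0.02 = 1.152; √(2.10/2.202) = 0.977; 2.2414 × 0.977 = 2.189; α = 0.0286.

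**5. Power of a test that does allow for runs.** Analysed per arm: 378 × 0.75 × 1.25 = 354.4. Effective sizes: 354.4/1.05 = 337.5 (control) and 354.4/DE_int (intervention).
Example, drinking, 6.75 families, ρ = 0.05: DE_int = 1.304, so 271.8 effective. Null SE 0.0403, alternative SE 0.0398. Without correction, Φ((0.12 − 2.2414 × 0.0403)/0.0398) = 77.2%. With correction, 0.12 is reduced by ½(1/337.5 + 1/271.8) = 0.0033, giving 74.6%.

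| ρ | True α | Drinking power, corrected (uncorrected) | Drunkenness power, corrected (uncorrected) |
|---|---|---|---|
| 0 | 0.025 | 80.1% (82.2%) | 87.0% (89.0%) |
| 0.01 | 0.027 | 79% (81%) | 86% (88%) |
| 0.02 | 0.029 | 77–78% (80%) | 85% (87%) |
| 0.05 | 0.034–0.036 | 73–75% (76–77%) | 81–82% (84–85%) |

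Ranges run over 6.75 to 7.9 families per run.

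**6. Check by simulation.** With a family-robust test, 48% prevalence and groups of 10 families, rejection rates under no effect were 0.027, 0.032 and 0.042 at ρ = 0, 0.02 and 0.05. The formula for groups of 10 gives 0.025, 0.031 and 0.040.

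**The case against.** The strongest objection is that everything depends on a quantity the article does not report. There are reasons to expect a small value: runs are composed to a similar mix of families, families do not normally come from one school or neighbourhood, exposure is seven sessions with the outcome at two years, and the model adjusts for area, family type, age and baseline behaviour. This stands. It rules out a flat statement that the p-values will be too small, and it argues against 0.10 as a working value. It does not justify fixing the value at zero, which is what the stated model does, when the article itself expects families in a run to affect one another.

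Three stronger readings are tempting and are not supported:

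- **That the stated power fails for both outcomes.** Drunkenness starts at 87–89% and stays above 80% up to ρ = 0.05 at these run sizes. On the uncorrected formula even drinking is still at about 80% at ρ = 0.02.
- **That the true level reaches 0.04 or more.** With ρ up to 0.05, that needs 10 to 12 families in every run. The article gives that range as a ceiling (though the Intervention section aims near it), and 56 full runs would need 560 to 672 intervention families against a target of 378.
- **That 378 is wrong.** It reproduces on its own inputs.

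The article's remarks on harmful peer modelling should not be used as evidence either. They concern targeted programmes, and the mixed-group model is meant to avoid that effect.

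**Conclusion.** The concern holds in conditional form. The stated primary models and power calculation omit a source of clustering that exists in one arm only and that the article expects to matter. Neither the area adjustment nor any listed repeat analysis covers it. If the run-level ICC lies between 0.01 and 0.05, with about 7 to 8 families per run, the nominal 0.025 becomes about 0.027 to 0.036. Drinking power becomes about 73–79% with continuity correction, or 76–81% without. On the corrected formula that yields 378, an ICC of about 0.001 is already enough to take drinking below 80%. Drunkenness remains adequately powered over that range.

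These figures assume equal run sizes, even loss to follow-up and a two-sided test. A reader might infer that significance is certainly overstated or that the trial is underpowered overall; without a run-level ICC the article does not support either. The effect is modest, but its direction is unfavourable and the correction is cheap, so it should be settled before outcome data are analysed.

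**What to change.** 1. In the primary and secondary models, use inference that allows for programme run in the intervention arm. The preferred form is standard errors clustered on programme run for intervention families and on family for controls, or a GEE with the same clusters.
2. If a partially nested mixed model is used instead, report the arm effect on the marginal scale. A random intercept in one arm only puts the two arms of a logistic model on different conditional scales. With equal 22% prevalence and ρ = 0.05, the conditional odds ratio comes out at roughly 0.94 to 0.95, depending on how the ICC is converted to the logit scale, although there is no effect.
3. Keep intervention families who never attend in the run they were offered, and record that run. The article describes routine attendance data but does not say that the offered run is held for non-attenders.
4. Restate the power for each outcome as conditional on a range of run-level ICCs, such as 0.01 to 0.05.

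The cost is a change of wording in the analysis plan, one recorded field, slightly wider intervals and a slightly less favourable power statement. No change to recruitment is proposed.

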### Randomisation

Families agreeing to participate in the research trial and who provide baseline data will be randomised using a computerised randomisation facility that will randomise families within strata defined by area (7) and use minimisation on the following variables:

• the category to which the family have been assigned (general population/family with challenges);

• age of children wishing to attend the programme (<12/12+). A mean will be taken if there is more than one child; and

• the number of children in the family wishing to attend the programme (1/>1).

There will be complete concealment of the randomisation sequence, set up securely within the randomisation database by the statistician, from the field recruitment staff and other trial team members. A random element, set at 80%, will also be used to increase the integrity and reduce the deterministic nature of the randomisation process.

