[90]. Thus we have specified two primary outcomes (related to drinking frequency and drunkenness frequency), alongside secondary and tertiary outcomes, and this is a strength of the trial design. The outcome measures map onto, and are designed to test a logic model for the programme developed by the research team, which has also driven the selection of short-term and intermediate outcomes. In this way the trial is assessing both the overall effectiveness of the SFP10-14, and its predicted causal pathways.

In order to maximise the external validity and utility of our findings we have adopted a pragmatic effectiveness trial design
[111,112], in which recruitment procedures and delivery systems replicate ‘real world’ implementation. Thus in our trial of SFP 10–14 UK the programme is provided by local agencies that are likely to implement it in the future, and the research team does not seek to impose inclusion criteria with the aim of reducing the heterogeneity of the trial population (as might happen in an explanatory trial which attempts to recruit homogenous groups of participants). Participating families therefore comprise children from across the 10–14 age band which the programme is aimed at (12–16 at follow-up), and it is possible that the SFP10-14’s potential impact on health behaviours such as alcohol could be patterned according to age.

The trial team will need to obtain support from local agencies delivering SFP 10–14 for the trial, many of whom may have little or no previous experience of running parenting/family/substance misuse prevention programmes as part of an RCT. Practitioners (and others) may object to random allocation on the grounds that they believe that the intervention is likely to be effective
[113], and that participants have unmet needs which SFP 10–14 UK addresses. Whilst central to many practitioners’ concerns may be the sense that participants randomised to the control condition are ‘given nothing’ (what Wong, et al. describe as ‘resentful demoralisation’ in the context of no treatment control groups)
[114], in pragmatic trials such as ours, both intervention and control group families continue to receive ‘care as usual’ (i.e. whatever services or programmes are usually available), though usual care/services may differ across trial sites. One potential response of practitioners to allocation of participants to a control group is to offer a compensatory package of treatment or support

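### The primary-model covariate list names two of the three minimisation factors and conflicts with the plan's own statement about all models

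*Protocol article*

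**What the plan says.** The Randomisation section stratifies by area (seven areas) and minimises on three variables:

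- family type: "the category to which the family have been assigned (general population/family with challenges");
- age: "age of children wishing to attend the programme (<12/12+). A mean will be taken if there is more than one child";
- number of children: "the number of children in the family wishing to attend the programme (1/>1").

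Main analysis says that the covariates in the two-level logistic models include those balanced at randomisation, and a bracket then gives them as type of family, "general population/family with challenges, and average age of young people". The baseline level of drinking or drunkenness is added, according to the outcome. Area has its own sentence: "Trial area (used as a stratification variable at randomisation) will be adjusted for".

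Further on, within the sentence on secondary analyses of tobacco and cannabis use, a parenthesis states that "all models will control for the variables that were balanced on at randomisation". The paragraph on educational and other outcomes again refers to the balanced variables without listing them.

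**The concern.** The bracket presents itself as the set of balanced factors but holds two of the three. An analyst who follows the bracket leaves number of children out of the primary model. One who follows the later parenthesis puts it in. Significance is declared at p < 0.025 for each outcome, and a combined test is triggered when both p-values fall between 0.025 and 0.05. A result close to either threshold could depend on which sentence was followed. The secondary and tertiary models point to the same balanced set, so they inherit the ambiguity.

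There is also a statistical reason to include every balancing factor. If a factor is related to the outcome and was balanced by design, a model without it ignores that balance. The test then tends to be slightly conservative and a little power is lost.

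**Working it through.** **1. The two lists side by side**

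| Factor | Randomisation | Named for the primary model |
|---|---|---|
| Area | stratified | yes, own sentence |
| Family type | minimised | yes |
| Age (family mean) | minimised, <12/12+ | yes, as average age |
| Number of children (1/>1) | minimised | no |

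Only number of children is affected.

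**2. The plan's sample size**

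The plan says: "We will aim to recruit 378 families in each arm of the trial". Inputs from the Sample size section: 48% against 36%, 2.5% level (taken as two-sided), 80% power, 1.25 young people per family, ICC 0.2, 25% loss.

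- Uncorrected n = [2.2414 × √(2 × 0.42 × 0.58) + 0.8416 × √(0.48 × 0.52 + 0.36 × 0.64)]² / 0.12² = 320.3.
- With continuity correction: (320.3/4) × [1 + √(1 + 4/(320.3 × 0.12))]² = 336.8, so 337 young people per arm.
- Design effect: 1 + (1.25 − 1) × 0.2 = 1.05.
- Families per arm: 337 × 1.05 / 1.25 / 0.75 = 377.4, so 378.

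The stated figure reproduces. It uses no covariate adjustment, so the choice of covariates does not change the required number.

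**3. Effect on the primary test**

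The document gives no covariate effects, so these are assumptions shown over a range. The simulation had 756 × 0.75 = 567 analysed families and about 1.25 children each. Ages were uniform from 10 to 15, 30% were families with challenges, and the latent sibling correlation was 0.2. Arms were balanced within number of children by mean age (<12/12+). The treatment log-odds ratio was −0.55. Models were logistic with family-clustered standard errors, tested at p < 0.025, with 600 runs per setting. All models were fitted to the same data sets.

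Power (%), with rejection under no effect (%) in brackets:

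| Assumed log-OR: per year of age; >1 child | Listed: average age, no number | Average age + number | Own age + number |
|---|---|---|---|
| 0.5; 0 | 72.0 (1.8) | 72.5 (1.8) | 72.2 (2.0) |
| 0.5; 0.3 | 75.8 (2.5) | 76.2 (2.5) | 75.8 (2.5) |
| 0.5; 0.8 | 69.7 (2.3) | 72.0 (2.5) | 71.8 (2.5) |
| 0.9; 0.3 | 67.7 (2.3) | 68.3 (2.3) | 68.7 (2.7) |

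- From the listed model to own age plus number, the gain is 0.2, 0.0, 2.1 and 1.0 points.
- Adding number of children alone gains 0.5, 0.4, 2.3 and 0.6 points. The 0.5 in the first row, where number of children has no effect, is 3 runs in 600 and is noise.
- Replacing average age by own age, with number already in, changes power by −0.3, −0.4, −0.2 and +0.4 points.
- Monte Carlo error is about 1.8 points for a single power figure, √(0.72 × 0.28/600), and 0.6 points for a null rejection rate, √(0.025 × 0.975/600). Differences within a row are more precise, because the data sets are shared.

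The power levels should not be read against the planned 80%. The simulated effect is smaller than the planned one: the unadjusted mean estimate was −0.425 in the first row, whereas 48% against 36% gives ln(0.36/0.64) − ln(0.48/0.52) = −0.575 + 0.080 = −0.495.

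**4. Standard errors**

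In the third row, adding number of children moved the mean estimate from −0.449 to −0.462 and the mean standard error from 0.1618 to 0.1629. The standard error rises slightly, but the ratio of estimate to standard error also rises, from 2.78 to 2.84. The listed model's cost is thus a slightly attenuated conditional estimate and a little power, not a wider standard error.

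**The case against.** The strongest reply is that nothing has been excluded. The covariates are said to include the balanced variables, which is not an exhaustive form of words, and the parenthesis about all models covers number of children. On that reading the bracket is merely incomplete, and a condensed article may leave the full list to the analysis plan. Part of this stands: the text does not show a settled decision to leave the factor out. But the article does not defer the list. It names the balanced factors, and the naming disagrees with its own Randomisation section. The parenthesis that would repair it sits in the secondary-analysis sentence, so its reach to the primary models is open to argument.

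A reader might also infer that family-average age is the wrong covariate for an individual outcome and costs real precision. Each young person's age is collected, and the Discussion says that impact "could be patterned according to age". If no family has more than two children, the 25% of families with two supply 0.5/1.25 = 40% of the young people. The document does not support that stronger reading. Average age is how the minimisation variable was defined, so adjusting for it follows the design. A separate simulation, with odds ratios of 1.5, 1.8 and 2.2 per year of age, gave power of 82%, 85% and 87% with age cut at 12, and 84%, 88% and 89% with continuous own age. Main analysis does not say that age will be cut, however, and the continuous family mean came within 0.5 points of own age.

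Nor should a reader infer that the listed model gives false-positive results or larger standard errors. Neither was seen.

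**Conclusion.** The point holds as an inconsistency in the stated primary model. One of three minimisation factors is missing from the covariate list, and another sentence in the same section implies that it belongs there. The listed model remains valid. Its likely cost is slight conservatism, too small to separate from simulation noise here, and a loss of 0 to about 2 points of power. Null rejection was 1.8% to 2.5% at a nominal 2.5%.

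These sizes rest on assumed effects of age (odds ratios of about 1.6 and 2.5 per year) and of having more than one child attending (odds ratios of 1 to about 2.2). The simulation used clustered standard errors in place of a two-level model, drew siblings' ages independently, and left out baseline drinking and area. The textual conflict needs none of these assumptions.

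**What to change.** State the primary-model covariates once, in full: family type, number of children attending (1/>1), age, trial area, and the baseline drinking or drunkenness measure that matches the outcome. Then say that the secondary models use the same balancing factors and area, each with its own baseline measure. The tobacco and cannabis models would keep baseline substance use, as already planned.

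Optionally, enter age as a continuous term using each young person's own age. This is a minor refinement, and keeping the family average is also defensible.

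The cost is one sentence. All the variables are already collected, and the sample size is unaffected. The wording should be settled before any outcome data are analysed.
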